### *Intervention*

Those in the intervention group will be provided with the activity tracker. During enrolment, participants will be guided through the process of turning off all of the notifications and messaging it provided. In addition, they will be helped to download the study support app (PaceMe) and guided through installation and the initial account registration and app onboarding. At enrolment, participants will be allocated time and heart rate (HR) limits of attempting to spend no more than 30 minutes per day above 60% of their age-predicted HRmax. Our separate server will then download the participants' HR for that day in 1-minute intervals from the Fitbit server and calculate the cumulative number of minutes above their HR threshold. The total number of minutes for that day will be displayed in the app, with data downloaded, processed and updated in the app approximately every 3 minutes.

Participants will also receive alert notifications when they reached 50, 75, and 100% of their time limits. Alerts include a text notification regarding the percentage of their time limit they have reached, as well as an infographic containing a suggestion for good pacing habits curated from responses from people with ME/CFS who had been using pacing for several years.

The app also allows participants to register when they experienced a bout of PEM. When this occurred, our server will review the 3-days prior to the bout and determine if they exceed their suggested pacing limits in any of those three days. If they had, then there will be no changes to their pacing limits, and participants will receive a notification that we had reviewed their data and that it was likely that they had experienced PEM because they had done too much. If participants had not exceeded their PEM limits, an algorithm will reduce either their HR or time limits, and participants will receive a notification that their bout of PEM might be because their limits were too high and that we had reduced them slightly.

### *App design and features*

To aid data collection the app also includes a series of validated instruments. As a result, in addition to logging a bout of PEM the app includes four 'sections' that participants will be requested to complete monthly: A 'symptom check in' to get a view of the month-by-month symptom load of participants. A 'brain-fog test' to assess cognitive function using the symbol digit modalities test. The remaining instruments will be split into two groups A and B, with

each group completed at a single point in time. Group A includes the Edinburgh Neurological Survey, the modified PEM questionnaire, and the SF12 quality of life assessment. Group B includes the MRC breathlessness scale, the EQ-5D-5L, PHQ4, the self-efficacy for long-term conditions, and the visual analogue pain scale. Data from each of the instruments will be stored in a GDPR-compliant data server. We also have the data server scan each participant's responses daily and send appropriate notifications to complete one of the four sections each week if responses are missing.

### *Control participants*

Those in the control group will continue with their usual care and follow any support services offered by their general practitioner or other long-COVID support services. Because the study also requires ongoing assessment of symptom load, PEM, and psychometric assessments, the control group will receive a version of the support app in which they could log a bout of PEM, and engage with each of the four sections of the app. They will also receive reminders to complete specific sections, but not receive any activity tracking, information on daily activity, nor any support messaging.

### *Measurement tools*

#### *PRIMARY OUTCOME*

##### *De Paul Symptom Questionnaire – Post-exertional malaise (DSQ-PEM)*

The baseline date will be considered as the date of baseline data collection. The DSQ-PEM is a 10-item questionnaire. Questions 1-5 are measured on a five-point Likert scale with a 'frequency' domain (0 = none of the time, 1 = a little of the time, 2 = about half the time, 3 = most of the time, and 4 = all of the time) and a 'severity' domain. (0 = symptom not present, 1 = mild, 2 = moderate, 3 = severe, and 4 = very severe). Questions 6-8 and 10 are dichotomous yes/no responses, and question 9 asked 'if you feel worse after activities, how long does this last?' with six options:  $\leq 1$  h, 2-3 h, 4-10 h, 11-13 h, 14-23 h, or  $\geq 24$  h. The DSQ-PEM sum is the sum of questions 1-5 (frequency and severity), expressed out of 100.

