## STUDY IMPLEMENTATION

### Protocol

Individuals expressing interest were contacted via telephone or video conferencing to arrange a briefing. This meeting included screening for inclusion and exclusion criteria, a verbal overview of the study and an opportunity to ask questions. Participants were provided with an information sheet and re-contacted at least 7 days later when they were provided with a further opportunity to ask questions and then, if willing, were enrolled on the trial. Once enrolled, participants provided their written informed consent to participate in the study and were allocated an enrolment number. A secure third-party service (Study-Randomizer) randomised participants into intervention or control groups stratified by age and sex with recruitment logs to ensure randomisation in recruitment order.

Following randomisation, a study start date approximately one week later was agreed. This provided time for an activity tracker (Fitbit Charge 5) to be posted to those allocated to the intervention group. Subsequently, in an online meeting, a study team member aided participants in downloading the PaceMe app from the relevant app store, ensuring they successfully registered an account and proceeded through the onboarding and digital consent screens. The app then asked for further participant information, including an activity tracker number for those allocated to the intervention group. The tracker number acted as a 'switch' such that participants who did not provide one were taken to the control version of the app, in which the home screen consisted of each of the questionnaires only. For those who did provide a tracker number, their home screen was an enhanced version of the PaceMe app, which included live metrics of their activity pacing for that day and over the previous days (see below).

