### *Randomisation*

Participants will be randomised to one of the two trial arms using 1:1 allocation ratio. Randomisation will be performed by a web-based online randomisation system (Study Randomizer). We will randomise participants remotely and participant blinding is impossible given the nature of the intervention.

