### *Statistical methods*

All analyses will be conducted using Jamovi version 2.3.21. Data will be tested for normal distribution and homogeneity of variance to confirm parametric assumptions are met. Data will be presented in text and tables as means and 95% confidence intervals (CI) unless otherwise stated. Because of randomisation, we did not undertake analysis of baseline equivalence, since the null hypothesis must be true and any differences due to chance . Only participants who completed follow-up testing were included in analysis (i.e. per protocol analysis). The effect of the energy management intervention on main and secondary outcomes will be examined using two-way mixed-model ANOVA with condition (intervention or control) as the between-subjects factor and time (pre- and post-intervention) as a within subjects' factor. Alpha level will be reported as exact p values and not described dichotomously as 'significant' or otherwise as recommended by the American Statistical Association . We will express effect sizes from the ANOVA as partial eta-squared ( $\eta^2p$ ), with values of 0.01, 0.06, and 0.14 interpreted as small, moderate, and large, respectively . For categorical data, (DSQ-PEM questions 6-10) we will use McNemar's Test for paired samples (pre- to post- intervention), or Chi squared test for between group effects (intervention vs. control).

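### The primary-outcome baseline is self-reported in the app after open allocation, with nothing tying it to a time before randomisation or tracker activation

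*Protocol*

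**What the plan says.** The order of events is under Study Implementation, Protocol. After consent and randomisation: "Following randomisation, a study start date approximately one week later was agreed". The reason given is logistic: "This provided time for an activity tracker (Fitbit Charge 5) to be posted to those allocated to the intervention group". App set-up comes next: "Subsequently, in an online meeting, a study team member aided participants in downloading the PaceMe app from the relevant app store". During set-up the arm is fixed in the app: "The tracker number acted as a 'switch' such that participants who did not provide one were taken to the control version of the app". Controls reach their questionnaires through that version's home screen.

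The Randomisation section states that "participant blinding is impossible given the nature of the intervention". The Intervention section sets the activity limits at enrolment.

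App design and features places the study instruments in the app. The PEM questionnaire belongs to Group A, one of four sections requested monthly. The server checks for gaps and will "send appropriate notifications to complete one of the four sections each week if responses are missing". The order of the sections is not given.

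The DSQ-PEM section defines timing in one sentence, repeated for every instrument: "The baseline date will be considered as the date of baseline data collection".

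Statistical methods specifies a two-way mixed ANOVA of condition by time and labels the first time point as preceding the intervention. On baseline comparability it says: "Because of randomisation, we did not undertake analysis of baseline equivalence, since the null hypothesis must be true and any differences due to chance".

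**The concern.** The DSQ-PEM is a self-report of symptom frequency and severity. A participant who has just learned that they will, or will not, receive the tracker may answer differently from one who does not yet know. An intervention participant who answers after the tracker and activity limits are live may also already have changed behaviour.

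A baseline fixed before allocation is protected from both influences. This one is protected from neither, although the analysis treats it as a pre-intervention value and uses it as the reference for the primary effect. The argument that baseline differences can only be chance holds for variables fixed before randomisation. It does not automatically hold for self-reports given after open allocation.

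**Working it through.** **1. Could the baseline precede allocation?** Setting the sections side by side:

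- Study Implementation puts app installation and the tracker-number switch after randomisation.
- App design and features puts the PEM questionnaire in the app.
- Randomisation says participants cannot be blinded.
- The Intervention section mentions app download during enrolment, but for people already in the intervention group.
- Ethical Considerations mentions an in-app signature, which fits the digital consent screens that Study Implementation places at app set-up.
- No section describes a DSQ-PEM before randomisation.
- The note to the baseline employment figure says the questionnaire was incomplete among the 125 per group, so at least that baseline item was not a condition of randomisation.

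By the described workflow, the baseline follows open allocation.

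**2. How late could it be?** With one section prompted per week and no order given, four weekly slots fall at weeks 0, 1, 2 and 3 after set-up. A reminder follows only a week after the due time, and no closing window is stated. Group A could equally be first, on set-up day.

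**3. How does a shift enter the estimate?** With two groups and two time points, the interaction tests

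(mean month 6 − mean baseline) in the intervention arm − (mean month 6 − mean baseline) in the control arm
= (month-6 difference) − (baseline difference).

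A baseline difference of δ points is subtracted point for point.

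**4. The plan's own sample size.** Inputs from Sample size and statistical power: f = 0.25, alpha 0.05, power 0.9, total 170. The test is noncentral F with df 1 and N − 2, and noncentrality N·f². At N = 170 the noncentrality is 170 × 0.0625 = 10.625 and power is 0.8999. The stated figure reproduces.

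**5. Late baseline (assumption: the effect builds linearly to 13 points over 26 weeks).** The share already present at week w is w/26, so f becomes 0.25 × (1 − w/26).

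| Weeks late | Points lost, 13·w/26 | Difference left | Power at N = 170 |
|---|---|---|---|
| 0 | 0 | 13.0 | 0.90 |
| 1 | 0.5 | 12.5 | 0.88 |
| 2 | 1.0 | 12.0 | 0.85 |
| 3 | 1.5 | 11.5 | 0.82 |

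The plan rounds 13/25 = 0.52 to d = 0.5. With d = 0.52 (f = 0.26), power is 0.92 at week 0 and 0.85 at week 3 (f = 0.26 × 23/26 = 0.23), so the loss is about the same.

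**6. Expectation shift (assumptions: no true effect, no month-6 difference, change SD 25).** With δ/SD as the standardised difference, f = δ/50.

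| Baseline shift between arms | Noncentrality, 170·f² | Two-sided rejection rate |
|---|---|---|
| 0 | 0 | 5% |
| 2 points | 0.272 | 8% |
| 3 points | 0.612 | 12% |
| 5 points | 1.700 | 25% |

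**The case against.** Several objections have force. The sentence dating the baseline is boilerplate attached to every instrument; alone it shows only that the definition is circular, and the evidence lies in the enrolment sequence. The prompting rule describes what happens when responses are missing and is not a baseline schedule. Linear onset has no source in the documents, 13 points is a minimum relevant difference and not a forecast, and the size of any expectation shift is assumed. Visit windows and sensitivity analyses are often left to an analysis plan, which is not shown. The protocol also tabulates completers, so re-ordering enrolment comes too late for those people.

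A reader might go further than the documents allow in three ways:

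- *That the baseline is contaminated.* No completion dates or shift are shown. The text supports only that it can be affected and that nothing prevents this.
- *That it was taken weeks into the intervention.* Group A may have been completed on set-up day with almost no exposure. A four-week delay would need Group A last plus a further lapse, so it is left out of the table.
- *That the problem can never be examined afterwards.* Recorded dates allow timing to be compared by arm, and month-6 scores can be analysed without the baseline.

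What stands is the order of events. Even a set-up-day baseline follows open allocation, so the expectation problem does not depend on the weekly prompts. Whether baseline is measured before or after allocation is trial conduct that the protocol fixes, and an analysis plan cannot create an earlier value.

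**Conclusion.** The concern holds as a gap in protection, not as demonstrated bias. The DSQ-PEM baseline is collected after open allocation and arm-specific app set-up, its date is tied to neither randomisation nor tracker activation, and the planned test passes any arm-specific shift into the primary estimate.

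Size and direction are unknown. Early benefit captured at baseline would shrink the estimate. Expectation could act either way, and a reporting shift of equal size at month 6 would cancel in the change score. Under the stated assumptions the late-baseline effect is modest (power 0.88 to 0.82 for 1 to 3 weeks), while an expectation shift of 2 to 5 points matters more (rejection rate 8% to 25% with no true effect).

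The statement that baseline differences must be due to chance is sound for variables fixed before randomisation and unsupported for questionnaires answered after it. Counting six months from randomisation in the hypotheses does not itself contradict the baseline definition, but the two should share one origin.

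**What to change.** For any further enrolment or re-use of this design:

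- Have participants complete Group A between consent and randomisation, using the tracker-free app version that already exists, and release the allocation only after submission.
- Define baseline as the last value before randomisation, and time month 6 from randomisation.

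For participants already randomised:

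- Report, by arm, days from randomisation to DSQ-PEM baseline and, in the intervention arm, days from tracker activation to baseline.
- Add a sensitivity analysis of month-6 DSQ-PEM scores that does not use the baseline. With d = 0.5 and SD 25, a two-mean comparison also needs 85 per group for 90% power, so the planned size supports it. It does not remove any expectation effect still present at month 6.
- Limit the statement about chance differences to variables fixed before randomisation, such as age and sex.

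The cost is one earlier app set-up step, with the tracker linked later for the intervention arm, and a few volunteers who never submit a baseline and so are not randomised. The analyses for enrolled participants need no new data collection, provided the app stored completion and activation dates.

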#### *SECONDARY OUTCOMES*

##### *Patient health questionnaire (PHQ-4)*

The baseline date will be considered as the date of baseline data collection. The PHQ-4 is a 4-item questionnaire (Kroenke, Spitzer, Williams, & Lowe, 2009). Questions 1-4 are measured on a four-point Likert scale with 0 = not at all, 1 = several days, 2 = more than half the days,

and 3=nearly every day. The PHQ-4 sum is the scores of each of the 4 items. Scores are rated as normal (0-2), mild (3-5), moderate (6-8) and severe (9-12). Total score  $\geq 3$  for first 2 questions suggests anxiety. Total score  $\geq 3$  for last 2 questions suggests depression.

#### *Fatigue severity scale (FSS-7)*

The baseline date will be considered as the date of baseline data collection. The FSS-7 is a 7-item questionnaire that measures the impact of fatigue (Krupp et al., 1989). Questions 1-7 are measured on a seven-point Likert scale with 1 (strongly disagree), 4 (neither agree nor disagree) and 7 (strongly agree). A visual analogue scale is also included with the scale; respondents are asked to denote the severity of their fatigue over the past 2 weeks by placing a mark on a line extending from “no fatigue” to “fatigue as bad as could be.” Higher scores on the scale are indicative of more severe fatigue.

#### *12-Item Short Form Survey (SF-12)*

The baseline date will be considered as the date of baseline data collection. The SF-12 is a 12-item questionnaire that measures self-reported health-related quality of life covering physical (PCS) and mental health (MCS) domains (Ware, Kosinski, & Keller, 1996). Question 1 is measured on a five-point Likert scale with 1=excellent, 2= very good, 3=good, 4=fair and 5=poor. Questions 2-3 are measured on a three-point Likert scale with 1=yes, limited a lot, 2=yes, limited a little, and 3= no, not limited at all. Questions 4-7 are measured are dichotomous yes/no responses. Question 8 is measured on a five-point Likert scale with 1=not at all, 2=a little bit, 3= moderately, 4=quite a bit, and 5=extremely. Questions 9-11 are measured on a six-point Likert scale with 1= all of the time, 2=most of the time, 3=a good bit of the time, 4=some of the time, 5=a little of the time, and 6=none if the time. Question 12 is measured on a five-point Likert scale with 1=all of the time, 2=most of the time, 3=some of the time, 4=a little of the time, and 5=none of the time. Scores above 50 indicate a better-than-average health-related quality of life, while scores below 50 suggest below-average health.

#### *EuroQol-5 Dimension (EQ5D)*

The baseline date will be considered as the date of baseline data collection. The study uses the EQ-5D-5L version to assess health status and produces a single index value for health status for use in the calculation of quality-adjusted life years to inform health economics evaluation of investigative interventions [10]. The instrument consists of an EQ-5D-5L descriptive system and an EQ-5D-5L visual analogue scale. The descriptive system has 5

dimensions assessing mobility, self-care, usual activity, pain/discomfort, and anxiety. Each of these dimensions has 5 levels of severity which participants are asked to select one of them to best describe their health status 'today': no problems, slight problems, moderate problems, severe problems, and extreme problems. Based on participants' responses from these 5 dimensions, a single index value will be calculated as detailed by Devlin et al [10]. The single index values are on a scale of 0 (full health) to 1 (state equivalent to dead) and health states considered to be worse than dead attain negative values ( $<0$ ).

#### *General self-efficacy scale (GSE)*

The baseline date will be considered as the date of baseline data collection. The GSE is a 10-item questionnaire to assess self-reported self-efficacy (Schwarzer, & Jerusalem, 1995). Questions 1-10 are measured on a four-point Likert scale with 1=not at all true, 2=hardly true, 3=moderately true, and 4=exactly true. The total score is calculated by finding the sum of all items. Total score ranges between 10 and 40 with a higher score indicating more self-efficacy.

#### *Breathlessness (MRC Dyspnoea scale)*

The baseline date will be considered as the date of baseline data collection. The MRC Dyspnoea scale is a 5-item questionnaire that assess the degree of baseline functional disability due to dyspnoea (Mahler, & Wellis, 1988). Questions 1-5 are measured on a four-grade scale with 0= I get breathless with strenuous exercise, 1=I get short of breath when hurrying on level ground or walking up a slight hill, 2=On level ground, I walk slower than people of my age because of breathlessness, or I have to stop for breath when walking at my own pace on the level, 3=I stop for breath after walking about 100 yards or after a few minutes on level ground, and 4= I am too breathless to leave the house or I am breathless when dressing/undressing. Total score ranges between 0 and 12 with lower scores indicating worse severity of dyspnoea.

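### The scoring rules for the MRC dyspnoea scale and the EQ-5D-5L index contradict themselves, so a change on either secondary measure could be read in the wrong direction

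*Protocol*

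**What the plan says.** Both rules stand in the protocol under Measurement tools, among the secondary outcomes.

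**MRC dyspnoea scale.** The section Breathlessness (MRC Dyspnoea scale) makes four statements about scoring:

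- Number of items: "The MRC Dyspnoea scale is a 5-item questionnaire".
- Response format: "Questions 1-5 are measured on a four-grade scale with 0= I get breathless with strenuous exercise". The list then runs on through grades 1, 2 and 3.
- The list ends at "4= I am too breathless to leave the house or I am breathless when dressing/undressing".
- Total and direction: "Total score ranges between 0 and 12 with lower scores indicating worse severity of dyspnoea".

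**EQ-5D-5L index.** The section EuroQol-5 Dimension (EQ5D) describes a "single index value for health status for use in the calculation of quality-adjusted life years". It sets the anchors as "The single index values are on a scale of 0 (full health) to 1 (state equivalent to dead" and adds in the same sentence that "health states considered to be worse than dead attain negative values".

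Three other places bear on the consequence. The breathlessness hypothesis is directional: the intervention is expected to improve it relative to usual care at six months. Statistical methods analyses main and secondary outcomes by a two-way mixed ANOVA, reported with means, 95% confidence intervals, exact p values and partial eta-squared. App design and features lists both instruments among those collected in the app.

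**The concern.** A scoring paragraph has to tell the analyst what values are possible and which end is bad. The MRC paragraph fails on both counts, because its closing sentence reverses the order of its own grades and gives a total that its own items cannot produce. The EQ-5D sentence fails on the second count, because its anchors and its remark on negative values cannot both be true.

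The stated direction matters more than usual here. The planned F tests and partial eta-squared carry no sign. Whether a difference between arms counts as the hypothesised improvement in breathlessness, or as better health on the EQ-5D index, is decided only by reading the means against the stated direction. A reader or programmer who relies on the MRC closing sentence or the EQ-5D anchors could report benefit as harm, or harm as benefit.

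**Working it through.** **1. MRC range.** The inputs are five items, a scale called four-grade, and listed grades 0, 1, 2, 3 and 4 (five grades). The formula is: maximum total = number of items × highest grade, with minimum 0. The target is the stated 0-12.

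| Reading of the text | Calculation | Range |
|---|---|---|
| One graded response, grades as listed | 1 × 4 | 0-4 |
| Five items, four grades (0-3) | 5 × 3 | 0-15 |
| Five items, grades as listed (0-4) | 5 × 4 | 0-20 |
| Stated in the protocol | – | 0-12 |

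The stated range is not reproduced. A maximum of 12 needs three items at 0-4 (3 × 4) or four items at 0-3 (4 × 3), and the paragraph describes neither.

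**2. MRC direction.** The lowest code is "0= I get breathless with strenuous exercise" and the highest is being too breathless to leave the house. Each step up describes more disability. Under every reading in the table the worst respondent therefore has the highest score (4, 15 or 20) and the least affected has 0. The closing sentence says the reverse.

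As an illustration, a participant who moves from grade 3 to grade 2 changes by 2 − 3 = −1. By the grade wording this is an improvement; by the closing sentence it is a deterioration.

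**3. EQ-5D anchors.** Take a state that lies 0.1 beyond dead on the line running from full health to dead.

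- Anchors as stated (full health 0, dead 1): 1 + 0.1 × (1 − 0) = 1.1. Worse than dead would exceed 1, and a value of −0.1 would lie on the better side of full health.
- Anchors exchanged (full health 1, dead 0): 0 + 0.1 × (0 − 1) = −0.1. Worse than dead is negative, as the protocol says.

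Only the exchanged anchors agree with the statement about negative values.

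**4. What is not affected.** Suppose a score y is reversed or rescaled to a + b·y. Every sum of squares in the mixed ANOVA is multiplied by b². The factor b² then cancels from F, and also from partial eta-squared, which is SS(effect) / [SS(effect) + SS(error)]. The p values and effect sizes are therefore unchanged; only the means, the confidence limits and their interpretation change.

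The SF-12 section states its direction consistently (above 50 is better). The primary DSQ-PEM score and the sample-size calculation use neither of the two instruments.

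**The case against.** The strongest reply is that each paragraph contradicts itself and does not lay down a consistently reversed rule. The MRC grade labels already imply that higher is worse, and the EQ-5D clause on negative values already implies that higher is better. The EQ-5D index is also to be computed by a cited published method, so the anchor sentence does not generate the values, and nothing in the protocol shows that the app or server scores either instrument wrongly. This stands. A reader might infer that both outcomes will certainly be reported with the sign reversed, but the document supports only a risk of misreading. The citation offers limited comfort: the bracketed number in the EQ-5D section is 10, and entry 10 in the reference list is a personal communication about a core outcome set, not a scoring method.

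Other stronger readings also go beyond the text:

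- **MRC effects understated threefold (12 against 4).** The factor needs the single-response reading and an effect divided by the scale range. Statistical methods plans no such division.
- **Quality-of-life results in general are compromised.** The SF-12, which App design and features labels as the quality-of-life assessment, is stated correctly. The protocol does not name the EQ-5D as the test of the quality-of-life hypothesis, so only the EQ-5D index is affected.
- **Inverted quality-adjusted life years will be reported.** They are mentioned as a use of the index, but no such analysis appears in Objectives, Secondary Outcome(s) or Statistical methods.
- **The ANOVA must be replaced by an ordinal model.** That is a separate preference; nothing in a direction or range error requires it.

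**Conclusion.** The point holds as an error in the stated scoring of two secondary measures. For the MRC scale the direction is reversed against the listed grades, the number of grades is misstated, and the 0-12 total fits none of the three readings that the text allows (maxima 4, 15 and 20). For the EQ-5D-5L index the two anchors are exchanged relative to the same sentence's own rule for negative values.

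These conclusions rest on the two paragraphs alone. They need no assumption about variance, dropout or alpha. That the MRC scale is a single 0-4 rating is likely, because the five descriptors form one ladder of severity, but the text does not settle it. The direction error and the impossible range hold either way.

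The consequence is limited to interpretation: the sign attached to a change in MRC score or EQ-5D index could be wrong if the text is followed. How the data were actually scored cannot be seen from the protocol.

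**What to change.** - **MRC.** State one scoring rule with a range that matches its grades: 0-4 if, as the descriptors suggest, it is a single graded response. State that higher is worse, correct the number of grades, and delete the 0-12 total.
- **EQ-5D-5L index.** State 1 = full health, 0 = dead, below 0 = worse than dead, higher = better. Correct the citation so that it leads to the scoring method.
- **Check.** Compare the scoring code and every table or figure of these two measures with the corrected text, and mark in each table which direction is better.

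The cost is two corrected paragraphs and one check of code and tables. The analysis model, the sample size and data collection stay as they are.
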